### Statistical analysis

Analyses will be conducted using SPSS, Stata, R, Mplus, AMOS, or equivalent software as appropriate for the final model specification. Descriptive analyses will summarize recruitment, baseline characteristics, retention, attendance, missingness, and adverse events. The primary effectiveness analysis should follow the intention-to-treat principle. Between-group change over time will be estimated using regression-based models or mixed-effects models that account for repeated measurements and baseline values. If families are nested within groups, facilitators, or municipalities, clustering will be considered in the model structure or sensitivity analyses.

Mediation or mechanism analyses may test whether changes in parenting practices, boundary setting, warmth, or conflict explain changes in child digital media-related outcomes. These analyses should be presented as exploratory unless the sample size and temporal ordering are sufficient for confirmatory causal mediation. Missing data will be examined, and multiple imputation or full-information maximum likelihood will be considered when assumptions are plausible. Qualitative data will be analyzed using reflexive thematic analysis [31] with procedures to support credibility, such as team coding, analytic memos, and discussion of discrepant cases.

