The original FAME program was developed for CAMHS (Child and adolescent psychiatry health services) as a group-based, family-centered intervention for children and adolescents with problematic gaming or excessive screen use and their parents aim at. It was informed by theoretical and empirical knowledge of parenting and child and adolescent development, findings from an earlier randomized trial of individual treatment for youth gaming problems, and interviews with parents about their support needs. FAME combines psychoeducation, cognitive restructuring, social-emotional learning, and parenting skills through an individual preparatory meeting followed by four group sessions for children and parents. The sessions address the positive and negative aspects of screen use and boundary setting, links between thoughts, feelings, and behaviors, conflict triggers and emotion regulation, and sleep hygiene [18].

However, the pathway through specialist child and adolescent psychiatry may be too narrow for families who experience screen-related conflict but do not require, or are not ready to seek, psychiatric treatment. This creates a prevention and service gap between general public health advice and specialist clinical intervention [18]. Together, these findings underscore the need for an intermediate, family-centered support pathway that is accessible, nonstigmatizing, and grounded in evidence. Although preventive programs targeting digital media use are emerging [10, 14], they generally focus on the child alone and do not address the broader family context. The present study is situated in that gap—between universal public health messaging and specialist psychiatric care—by evaluating S-FAME (where S stands for Social services) as a structured, family-centered program delivered within Swedish municipal social services.

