### Study design

This protocol describes a 2-arm, parallel-group randomized controlled trial with embedded implementation, qualitative, and health economic components. Families will be randomized to immediate S-FAME or to a comparator pathway consisting of treatment as usual during the study period and later access to P-FAME (Parental- Family-Centered Treatment Program for Problematic Gaming and Excessive Screen Use in a Clinical Child and Youth Population), a brief online parent intervention. Six social services units across participating municipalities have endorsed the project and will support implementation procedures.

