### Recruitment and eligibility

Families will be recruited through participating municipal social services when parents or children seek support for repeated digital media use conflict, impaired routines, parental concern, or child functioning problems. The target group is families who experience digital media-related difficulties severe enough to seek structured support from social services. Based on power analyses appx 176 participants will be required to detect a small effect size (d = 0.03), accounting for potential attrition. Eligible families must include a child aged 10–14 years; at least one parent or legal guardian willing to participate (note: both child and parent participation is required for S-FAME delivery); reported concern related to gaming, social media use, other digital media activities, or screen-related family conflict; and sufficient Swedish language ability to participate in sessions and complete measures. Families will be excluded when acute safeguarding concerns, severe psychiatric instability, ongoing crisis, or another service need makes participation in a group-based preventive intervention inappropriate.

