### Randomization and control group

After consent, eligibility confirmation, and baseline assessment, families will be randomized in a 1:1 ratio to immediate S-FAME or the comparator pathway. Allocation will be concealed from the assigning researcher until after eligibility confirmation and baseline assessment, using a centralized randomization procedure (e.g., sealed envelopes or web-based allocation). The control group will receive regular support from social services (treatment as usual) during the study period, reflecting ordinary municipal routines available to families. After the study period, families in the control group will be offered P-FAME, a three-session online intervention for parents. This delayed parent-focused offer is included for ethical and practical reasons and should be described consistently as part of the control condition rather than as the same intervention as S-FAME.

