### Qualitative and implementation evaluation

The qualitative component will examine more than satisfaction with the program. It will investigate how families understand the offer of support from social services, whether S-FAME feels accessible and non-stigmatizing, how children and parents experience joint participation, and which parts of the program are most useful or difficult to apply at home. Approximately 15 to 20 children and 15 to 20 parents will be interviewed by trained research assistants [27] within one month after participation, with final sample size guided by information power and thematic saturation.

Focus groups with social workers and group leaders will examine implementation fit, training needs, fidelity, perceived appropriateness for the target group, burden on ordinary services, safeguarding boundaries, and the feasibility of offering S-FAME without a prior individual needs assessment when legally and locally appropriate. Notably, it is necessary to understand whether the model can become part of routine municipal preventive work.

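### S-FAME families are nested in treatment groups by design, but the plan makes clustering conditional and lets it be handled only in sensitivity analyses

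*Protocol article*

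**What the plan says.** Three places in the protocol article show group delivery. Recruitment and eligibility excludes families when "another service need makes participation in a group-based preventive intervention inappropriate". Qualitative and implementation evaluation plans the following: "Focus groups with social workers and group leaders will examine implementation fit". The Introduction describes the parent FAME programme as "an individual preparatory meeting followed by four group sessions for children and parents".

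Allocation is by family. Under Randomization and control group, "families will be randomized in a 1:1 ratio to immediate S-FAME or the comparator pathway". The same section describes the comparator: "The control group will receive regular support from social services (treatment as usual) during the study period". It mentions no shared groups for that arm.

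The rule on clustering is one sentence under Statistical analysis: "If families are nested within groups, facilitators, or municipalities, clustering will be considered in the model structure or sensitivity analyses". The only structure to which that section commits the effectiveness model is repeated measurements and baseline values. The sample-size sentence under Recruitment and eligibility allows for attrition but mentions no group size, ICC or design effect.

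**The concern.** Families who attend the same sessions, with the same leaders and the same other families, tend to have correlated outcomes after treatment. Individual randomization does not remove this, because the correlation arises after allocation. As described, it arises in the S-FAME arm only, so the design is partially nested.

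The clustering sentence is loose in three ways. Its condition is already met at the group level by the programme's own format. It promises consideration, not a method. It also allows the adjustment to sit outside the primary model.

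A primary analysis that ignores groups would understate the variance of the S-FAME mean, give an interval that is too narrow, and raise the chance of a false claim of effectiveness. That claim has a further consequence: under Health economic evaluation, the incremental cost-effectiveness analysis is carried out only if the primary outcomes show a statistically or clinically meaningful difference.

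**Working it through.** **Inputs from the article.** At least 176 families are randomized 1:1, so 176 / 2 = 88 per arm. Randomization is by family, and groups exist in the S-FAME arm.

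**Inputs assumed, because the article gives none.** Group size m is 4 to 10 families, which gives 88/4 = 22 groups down to 88/10, or about 9. The ICC is 0.01 to 0.10, read as the within-group correlation of the outcome as analysed. Groups are of equal size, total variance is equal in both arms, and control families are independent.

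**The plan's own figure.** The article gives no clustering figure to reproduce. Its 176 does not follow from the printed d = 0.03: with an assumed two-sided 5% test and 80% power, that effect needs 17,442 per arm. This is a separate issue and nothing below depends on it. Only the 88 per arm is used.

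**Formulas.**

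- Design effect in the S-FAME arm: 1 + (m − 1) × ICC. In the control arm it is 1.
- Variance of the difference relative to independence: the mean of the two, 1 + (m − 1) × ICC / 2.
- True SE / naive SE: the square root of that.
- Actual two-sided type I error of a nominal 5% test: 2 × [1 − Φ(1.96 / SE ratio)].

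**Example, m = 8 and ICC = 0.05.** The variance ratio is 1 + 7 × 0.05 / 2 = 1.175. The SE ratio is √1.175 = 1.084. The type I error is 2 × [1 − Φ(1.96 / 1.084)] = 0.071.

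| m | ICC | Variance ratio | SE ratio | Type I error (formula) |
|---|---|---|---|---|
| 4 | 0.01 | 1.015 | 1.007 | 0.052 |
| 4 | 0.05 | 1.075 | 1.037 | 0.059 |
| 4 | 0.10 | 1.150 | 1.072 | 0.068 |
| 8 | 0.01 | 1.035 | 1.017 | 0.054 |
| 8 | 0.05 | 1.175 | 1.084 | 0.071 |
| 8 | 0.10 | 1.350 | 1.162 | 0.092 |
| 10 | 0.01 | 1.045 | 1.022 | 0.055 |
| 10 | 0.05 | 1.225 | 1.107 | 0.077 |
| 10 | 0.10 | 1.450 | 1.204 | 0.104 |

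**Check by simulation.** A t-test that ignores groups was run 40,000 times per setting, with 88 per arm and no treatment effect.

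- At ICC 0, the rejection rate was 0.049 (m = 4) and 0.048 (m = 8).
- At ICC 0.05, it was 0.061 (m = 4) and 0.069 (m = 8).
- At ICC 0.10, it was 0.069 (m = 4) and 0.093 (m = 8).

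These agree with the formula.

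**Effect on power when clustering is handled correctly.** A test sized for 80% power under independence has power Φ[(1.96 + 0.842) / SE ratio − 1.96]. That is 79% at m = 4, ICC 0.01; 73% at m = 8, ICC 0.05; and 64% at m = 10, ICC 0.10. To keep the precision of 176 independent families, the total is 176 × variance ratio: 179, 207 and 256 respectively.

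**The case against.** The strongest reply is that the sentence also permits the right analysis. Putting clustering into the model structure is one of its two options, so no error is yet fixed in the primary model. This stands: a reader might infer that the primary standard error is already too small, and the text does not support that. The error arises only if the other option is chosen and the ICC is positive.

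A second reply is that this is a condensed article and that model detail belongs in the analysis plan. This stands for the random-effects structure, the residual variances and the degrees of freedom. It does not cover the rule itself, which the article states, makes conditional on something its own design settles, and leaves open to an invalid choice.

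Third, the article does not say that control families are ungrouped. It says only that they receive ordinary support, and under Limitations it warns that this may vary between municipalities. This stands, and the remedy must allow for it.

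Fourth, a reader might extend the argument to municipality and object that six levels are too few for a random effect. Neither part is supported. Municipality is crossed with arm under individual randomization, so omitting it does not in general shrink the standard error of the treatment effect. The article says "Six social services units across participating municipalities have endorsed the project", which counts units and does not give the number of municipalities. The argument reaches facilitators only if they deliver S-FAME alone, which the article does not state.

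Last, at ICC 0.01 the effect is negligible whatever the group size. This stands too.

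**Conclusion.** The point holds as a should-fix. Nesting in treatment groups is part of the S-FAME design, and the stated rule allows a primary analysis that ignores it. If that option were taken with a positive ICC, the naive standard error would be 0.7% to 17% too small and the type I error about 5.2% to 10.4%, over groups of 4 to 10 families and an ICC of 0.01 to 0.10 with 88 per arm. A middle case, groups of 8 with an ICC of 0.05, gives about 7%. The direction is certain for any positive ICC. The size is not, because the article gives neither input. The figures also rest on equal group sizes, equal total variance in the two arms and independent control families.

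**What to change.** Replace the clustering sentence with text such as:

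> Families in the S-FAME arm are nested in treatment groups. The primary model accounts for this through a random group effect in the S-FAME arm, with each control family as its own cluster unless treatment as usual is itself delivered in groups, and with a small-sample correction. A model that ignores groups is a sensitivity analysis.

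Another valid method that accounts for groups in the primary analysis would also serve. The exact degrees-of-freedom method and whether residual variance differs by arm can be left to the analysis plan. The small-sample correction matters because the assumed group sizes imply only about 9 to 22 groups.

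Record the group and facilitator for every S-FAME family as groups run. Recruitment is planned for February to December 2026, and these fields are harder to reconstruct afterwards. Record also whether any treatment as usual is given in groups. When the power figure is restated, give the assumed group size and ICC.

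The cost is a change of wording, one or two data fields and slightly wider intervals.

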### Ethical considerations

SPIRIT items 24–26 – Ethics and consent: Ethical approval, consent procedures, and participant confidentiality are described in this section. SPIRIT item 29 – Declaration of interests: See Conflicts of Interest. SPIRIT item 31 – Protocol amendments: Any future amendments will be submitted to the Swedish Ethical Review Authority and registered on ClinicalTrials.gov (NCT07245862). See Appendix X for the complete SPIRIT checklist.

Participation is expected to involve low risk but may include discussion of family conflict and sensitive routines. Written and verbal information will be provided to children, parents, and participating professionals. Consent and assent procedures will follow Swedish ethical requirements, including guardian consent for children younger than 15 years and attention to the child’s age and maturity. Participation will be voluntary, and families may withdraw without consequences for ordinary social services support.

Data will be pseudonymized or deidentified and stored securely according to the General Data Protection Regulation and the ethical approval. Ethical approval has been granted by the Swedish Ethical Review Authority (Dnr 2025-05262-01; September 29, 2025).

## Results

Recruitment is planned to begin in February 2026 and end in December 2026. Final quantitative, qualitative, implementation, and health economic analyses are planned for the first quarter of 2027 after completion of follow-up assessments, data validation, and qualitative coding.

## Discussion

### Principal expected contribution

The principal contribution of this trial is the evaluation of whether a family-centered intervention targeting multiple members of the family network — specifically children and parents — reduces screen-related child problems, family conflicts, and improves overall family functioning [7, 8]. In addition, the trial is expected to clarify to what extent improvements in child screen-related functioning occur alongside changes in parenting practices and parent-child relationships. Moreover, this trial will also generate implementation knowledge about staff training, recruitment, family engagement, fidelity, and adaptation across municipalities.

The trial is expected to clarify whether improvements in child screen-related functioning occur alongside changes in parenting practices and parent-child relationships. It will also generate implementation knowledge about staff training, recruitment procedures, family engagement, fidelity, and adaptation across municipalities. These elements are essential for establishing whether a family-centered model can be delivered with fidelity and at scale within ordinary municipal social services constraints.

### Limitations

Potential limitations include recruitment, reliance on self-report measures, short follow-up, variation in municipal implementation, and possible differences between families who seek support and those who do not. The comparator pathway may also vary across municipalities if treatment as usual is not standardized. These limitations should be addressed by transparent reporting of local procedures, monitoring of implementation fidelity and adaptations, and sensitivity analyses when feasible.

## Conclusions

S-FAME represents a family-centered, low-threshold intervention designed for delivery within Swedish municipal social services. By evaluating its effectiveness, implementation feasibility, and health economic consequences in a randomized controlled design, this study addresses a critical gap in the evidence base for preventive support for children and families experiencing digital media-related difficulties. The findings will inform how municipalities can provide early, accessible, and non-stigmatizing family support before problems escalate to require specialist psychiatric care. If effective and feasible, S-FAME has the potential to be scaled across Swedish municipalities and to contribute to the broader evidence base for preventive family-centered interventions in social services.

## Data Availability

No datasets were generated or analysed during the current study.

## Abbreviations

CAP: Child and Adolescent Psychiatry
CBA: Cost-Benefit Analysis
CEA: Cost-Effectiveness Analysis
FCU: Family Check-Up
GSMQ-9: Gaming and Social Media Questionnaire
HBSC: Health Behaviour in School-aged Children
ICD-11: International Classification of Diseases, 11th Revision
IGD: Internet Gaming Disorder
ISI-A: Insomnia Severity Index for Adolescents
PARCA: Parenting Children and Adolescents Scale
P-FAME: Parent-focused Digital FAME Intervention
RCT: Randomized Controlled Trial
SEM: Structural Equation Modeling
S-FAME: Social Services Family-Centered Program for Digital Media–Related Family Difficulties
SPIRIT: Standard Protocol Items: Recommendations for Interventional Trials
WHO: World Health Organization
